### Allocation, randomization and sequence generation

After baseline tests and surgery the patients will be randomized equally (1:1) to receive either the PR protocol or the UC protocol. The computer-generated randomization to one of two treatment arms is performed based upon permuted random blocks of variable size (4–8 in each block) using the Procordo Research Platform. To counter potential imbalance in the randomization, stratification by trial site and age (+/− 57 years) will be employed together with blocking. The randomization is performed by a person (SW) with no clinical involvement in the trial, and the person notifies the patient and clinical study staff of the treatment allocation. The allocation will be concealed in a password-protected Research Platform only accessible by the senior researcher and the independent data manager (Procordo).

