The Danish National Clinical Guideline on selected shoulder disorders recommends that these patients are offered rehabilitation after surgical repair, and that the shoulder is immobilized post-surgery (usual care) [14]. However, the existing clinical studies of postoperative treatment targeting patients with rotator cuff repair are of moderate to low quality (lack of blinding, small sample sizes, lack/poor responsiveness on outcomes, and/or with only per protocol analyses) [15–20], making it difficult to unequivocally conclude what treatment regimen is the best. Studies on the timing of rehabilitation have showed a smaller positive short-term effect of early active rehabilitation (from postoperative day 21) compared to later rehabilitation [15], but no superior effect of early passive exercises [17, 19, 20]. A small or no effect was seen in studies focusing on the intensity of rehabilitation, including passive exercises versus immobilization [16] and progressive versus limited early passive exercises [18]. Recent systematic reviews on the effect of rehabilitation after rotator cuff surgery confirms that early range of motion (ROM) exercises accelerate healing, reduce stiffness, do not increase the risk of re-tear and that immobilization does not increase tendon healing or the clinical outcome [21–24]. However, high-quality and adequately powered trials with standardized treatment protocols testing early initiation of rehabilitation and gradual introduction of functional load and including important clinical outcomes such as return to work are needed [25, 26].

Research on rotator cuff tears often focuses on improvement of surgery techniques [9, 27–31], biomechanics and biology of tendon healing [16, 32, 33]; however, little is known about the effects of postoperative rehabilitation. Human autopsy studies indicate that the tendon can regain its ability to transmit almost the same amount of force as an intact tendon if it is fully repaired [10, 33]. The magnitude of retraction will markedly influence the rotator cuff muscle generating capacity [33]. Based on autopsy and physiological data [34] it has been suggested that rehabilitation should include reestablishment of joint ROM, shoulder function and muscular strength while considering the healing time of the repaired tendon.

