### Patients and settings

Patients are recruited from the Section for Sports Traumatology, Department of Orthopedic Surgery, Bispebjerg-Frederiksberg Hospital and from The Shoulder-Elbow Unit, Herlev-Gentofte Hospital, both in Denmark. Additional inclusion sites may be added.

Patients may be enrolled in the study provided they meet all of the inclusion criteria:Age minimum 18 yearsA clinical diagnosis of traumatic full-thickness rotator cuff (RC) tear involving the supraspinatus tendon (full thickness and width) verified by arthroscopyA repairable tear

In trauma the trauma mechanism should be described. Typically it will be a forced abduction and external rotation to mitigate for a fall, a fall on the outstretched arm, a pull in the arm or a shoulder luxation. No previous symptoms are implied within the definition of a traumatic tear.

Patients are excluded if they fulfill any of the following exclusion criteria:A non-traumatic RC tear of the shoulderAn isolated teres minor or subscapularis tearA partial-thickness/partial-width tearPrior shoulder surgery (all shoulder joints)A clinical diagnosis of glenohumeral osteoarthritis (OA), rheumatoid arthritis or periarthrosisUnable to speak or read DanishUnable to perform and maintain the exercise therapyOther conditions that negatively influence compliance, or place the patient at increased risk, or otherwise make them unsuitable for participation

Orthopedic surgeons perform an initial screening of all patients referred to the department for surgery. If the patients fulfill the eligibility criteria they are referred to the principal investigator, who performs the final eligibility assessment, give the patient detailed information about the study and ask for consent to participate in the study. If the patient consents to participate a baseline assessment visit is performed between 1 and 14 days before surgery, on the understanding that the patient is not finally included and allocated until the surgeon verifies a total and repairable supraspinatus tear. After surgery the orthopedic surgeon provides surgery information (verifying reparable tendon (s)), and included patients are electronically randomized (described in “Allocation, randomization and sequence generation”).

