Thus, the US investigation at 12 months involves quantitative measures of the repaired and contralateral SST thickness and neovascularity (NV), in addition to the SAS measured as the acromiohumeral distance (AHD). Ultrasound images are captured with the patients seated in an upright position, feet flat on the floor, neutral trunk posture, and head facing forward. For the SST thickness measure the patient has the hand on the affected side on the ipsilateral posterior hip with the humerus in extension and the tendon is measured in a longitudinal [72] and a transverse view [67]. AHD is measured in the neutral position (arm resting at the side) and respectively with 45° and 60° of active shoulder elevation in the scapular plane [72, 73]. SST neovascularity assessed by power Doppler is measured with the shoulder internally rotated with the dorsal side of the hand placed on the sacrum, and the elbow flexed and directed laterally [74].

Registered demographic data include age, gender, tendon(s) involved, supplementary surgery performed, hand dominance, history of trauma, occupation/employment and preoperative sports/recreational activity level. Demographic data and baseline measures will be used in the analysis of predictors of health outcomes.The investigator or site personnel monitor each patient for adverse events (AEs) throughout the study. Tendon re-tear is assessed by US at 6 weeks postoperatively and any re-tear is recorded. The investigator assesses and records any AE (in response to a query, observed by site personnel or reported spontaneously by the patient) in detail, including the date of onset, description, severity, duration and outcome, relationship of the AE to study intervention and any action(s) taken. All AEs will be followed closely to make sure that the patient is safely handled including follow up on clinical issues, until a stable situation is reached.

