The primary analysis at week 12 will be by analysis of covariance (ANCOVA) on change from baseline in the WORC domains as dependent variables, with group allocation (two levels) and time (week 6 and 12), gender and site as fixed factors, whereas age and baseline values will be analyzed as covariates. Secondary outcome measures will be analyzed by multiple logistic regression for binary outcome measures (re-tear, tendon healing, recurrence of symptoms (e.g. pain and function), complications) and by ANCOVA for the continuous outcome measures (pain, patient-reported outcomes, surgery information, strength, ROM) as dependent variables (individually), with group allocation and time as fixed factors, and site and baseline values as covariates. Predictors of health outcomes will be analyzed by ANCOVA or multiple regression as independent variables, with change in the WORC as the dependant variable. All statistical tests will be two-sided and statistical significance will be denoted by a computed *p* value equal to or less than 0.05. All data analysis will be carried out according to a pre-established analysis plan. The statistical analysis plan (SAP) will be carried through blinded according to group allocation, and results will be interpreted in an author consensus statement prior to disclosing/revealing group allocation on the basis of a blinded review of the data from the primary endpoint (changes from treatment A compared to changes from treatment B), assuming that treatment A is the active treatment (PR), and the other assuming that treatment B is the active treatment (UC). Analysis of the primary outcome will be calculated blinded, and two interpretations will be performed based on whether PR or UC is superior. Not until signed consent from all of the authors of this trial (identical to the authors of this SAP) has been obtained, agreeing on one interpretation of the results only, will the randomization code be broken. This is to reduce bias in the interpretation of the current findings. On agreement, all members of the author group will approve and sign the interpretations before any publication procedures are initiated [76].

The protocol conforms to the recommendations of the Enhancing the Quality and Transparency Of health Research (EQUATOR) network [77] using the Standard Protocol Items: Recommendations for Interventional Trials (SPIRIT) checklist and the Consolidating Standards of Reporting Trials (CONSORT) statement [78] (Additional file 3).

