## Discussion

The effect of rehabilitation after rotator cuff surgery has been discussed during the past 10 years and 13 systematic reviews including meta-analyses or systematic review of overlapping meta-analyses have been published since 2014 including the same few (8–12) primary studies [21–26, 81–87]. These have focused on early ROM exercises and immobilization periods. Nevertheless, there are only a few clinical studies on postoperative treatment of individuals with rotator cuff repair and the existing studies are of moderate to low quality. This is primarily due to small sample sizes, inadequate blinding of patients and/or investigators and incomplete intervention descriptions [15–20], making it difficult to transform the results into clinical practice. Furthermore, previous studies use a wide range of clinical and patient-reported outcomes, generally with poor responsiveness and per-protocol analyses. However, collectively there is evidence that early intervention is advantageous in the rehabilitation because early ROM exercises accelerate healing, reduce stiffness, do not increase risk of re-tear, and because immobilization does not increase tendon healing or clinical outcome [21–24].

The CUT-N-MOVE trial will add new knowledge to the field with regards to the effect of an early and targeted progressive treatment program for patients who had surgery due to a rotator cuff tear. To our knowledge this study is the first evaluating the combined effect of early (time of initiation) and progressive (intensity, also including active muscle contraction) postoperative exercises on parameters such as physical function, pain, quality of life and return to work.

Inclusion criteria in this study are broad with respect to age and concurrent diseases in an attempt to reflect clinical practice. However, inclusion criteria are narrow regarding the specific condition, and thus we require the tears to be based on relevant extrinsic trauma and at the least a complete supraspinatus tear must be verified during surgery/arthroscopy.

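### Tear extent is known before randomisation and varies by design, but the stated primary WORC ANCOVA does not adjust for it: an optional, cheap gain in precision

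*Protocol article*

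**What the plan says.** **Eligibility.** Patients and settings (Protocol article) requires a repairable traumatic full-thickness, full-width supraspinatus tear and, by tendon, excludes only teres minor or subscapularis tears that are isolated. The Discussion confirms that this is a lower limit: "at the least a complete supraspinatus tear must be verified during surgery/arthroscopy". Supraspinatus tears that extend to another tendon are therefore eligible if repairable.

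**Timing and recording.** Patients and settings: "After surgery the orthopedic surgeon provides surgery information (verifying reparable tendon (s)), and included patients are electronically randomized". Outcome measures/variables: "Registered demographic data include age, gender, tendon(s) involved, supplementary surgery performed, hand dominance". The next sentence gives the use of these data: "Demographic data and baseline measures will be used in the analysis of predictors of health outcomes".

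**Randomisation.** Allocation, randomization and sequence generation: "stratification by trial site and age (+/− 57 years) will be employed together with blocking".

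**Analysis.** The Statistical analysis plan section gives the primary ANCOVA group and time, with "gender and site as fixed factors, whereas age and baseline values will be analyzed as covariates". For continuous secondary outcomes it names group, time, site and baseline values. It places information from surgery among the continuous dependent variables. The multiple-imputation predictors are age, gender, centre, masked group and baseline values. Tear extent is in none of these lists.

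**The concern.** Eligibility leaves the number of torn tendons open upward, and that number is known before allocation. It is thus a legitimate baseline covariate, already collected. The protocol regards it as a possible predictor of WORC change but does not use it when comparing treatments. Pre-operative WORC may carry part of the information, but the repair itself is established only at arthroscopy.

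The Background also gives structural severity some weight: "The magnitude of retraction will markedly influence the rotator cuff muscle generating capacity". That sentence concerns retraction and muscle capacity, so it bears most closely on strength and only indirectly on tendon count or 12-week WORC.

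Two things are at stake. If tear extent is prognostic, leaving it out wastes some precision. If the arms happen to differ in it, the stated model does not correct for that, and an adjustment added after the imbalance has been seen would be open to challenge. Separately, operative findings precede allocation, so comparing them by arm as an outcome can only describe the randomisation.

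**Working it through.** **1. The plan's own figures.** Inputs from Sample size and power considerations: difference 12, SD 20, significance level 5% (two-sided per the Statistical analysis plan section).

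- n per arm for 80% power = 2 × (1.960 + 0.842)² × 20² / 12² = 43.6, so 44 (45 with the t distribution). The stated 41 is not reproduced.
- Power at 41 per arm: 77.5% (normal), 76.5% (noncentral t).
- Power at 50 per arm: 85.1% (normal), 84.4% (noncentral t). The stated 85% is reproduced.

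The shortfall at 41 is a separate matter. Here 76.5% serves only as the reference value.

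**2. Assumptions.** The documents give neither the share p of multi-tendon tears nor their deficit g in WORC improvement. I take p = 30–50% and g = 5, 10 or 15 points. Tear extent is treated as unrelated to the other model terms. If baseline WORC absorbs part of it, the gain is smaller.

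**3. Chance of imbalance** (exact hypergeometric, equal arms, p = 30–50%):

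| Per arm | Arms differ by ≥10 points | ≥15 points | ≥20 points |
|---|---|---|---|
| 50 | 27.5–31.7% | 12.6–16.1% | 4.9–7.1% |
| 41 | 33.7–37.7% | 14.9–18.5% | 5.4–7.7% |

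**4. Shift in the unadjusted difference** = imbalance × g.

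- Smallest: 0.10 × 5 = 0.5 points (0.5/12 = 4% of the target).
- Largest: 0.20 × 15 = 3.0 points (3/12 = 25% of the target).
- For scale, the standard error at 50 per arm is 20 × √(2/50) = 4.0, so 3 points is 0.75 standard errors.

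**5. Precision gained.** R² = p(1 − p)g²/20²; residual SD = 20 × √(1 − R²); n by the normal formula; power by the noncentral t.

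| p | g | R² | Residual SD | n per arm for 80% | Power at 41 per arm |
|---|---|---|---|---|---|
| 30% | 5 | 0.0131 | 19.87 | 44 | 77.1% |
| 30% | 10 | 0.0525 | 19.47 | 42 | 78.7% |
| 30% | 15 | 0.1181 | 18.78 | 39 | 81.5% |
| 50% | 5 | 0.0156 | 19.84 | 43 | 77.2% |
| 50% | 10 | 0.0625 | 19.36 | 41 | 79.2% |
| 50% | 15 | 0.1406 | 18.54 | 38 | 82.5% |

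At the weak end the gain is nearly nil; at the strong end it is worth about six patients per arm (44 − 38).

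**6. Does imbalance alone reach the stopping rule?** Assume re-tear in 10% of single-tendon and 30% of multi-tendon tears, and an overall multi-tendon share of 40%. A split of 50% v 30% gives (0.10 + 0.20 × 0.50)/(0.10 + 0.20 × 0.30) = 0.20/0.16 = 1.25. A ratio of 2 needs 70% v 10%, that is 0.24/0.12, a difference of 60 percentage points. Chance imbalance of plausible size does not get there.

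**The case against.** Randomisation already makes the stated analysis valid. Omitting a prognostic covariate leaves the estimate unbiased over repeated randomisations and does not inflate type I error; the confidence interval allows for chance imbalance. Site and age are ordinary strata for 100 patients. Every input to the size of the gain is assumed, and at the weak end nothing is gained. Further covariates and baseline tables might sit in an analysis plan that is not shown. All of this stands, except that the article lists the terms of its primary model explicitly, so adding one changes a stated model rather than supplying detail left to another document.

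A reader might infer four stronger things that the documents do not support:

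- **That tear extent is absent from every model.** It is available to the planned analysis of predictors of WORC change. That analysis does not adjust the treatment comparison, but it exists.
- **That tear extent is the chief source of heterogeneity.** The Discussion calls the criteria broad for age and concurrent disease and narrow for the condition itself.
- **That imbalance could trigger the early stopping rule.** The rule needs a re-tear rate more than twice that in usual care, and step 6 falls well short. It also compares raw rates, so a covariate would not alter it.
- **That the re-tear model wrongly omits the factor.** The article does not make clear whether the listed covariates extend to the logistic models, and re-tears may be few. At the assumed rates, 30–50% multi-tendon gives 16–20 events in 100 patients (100 × (0.10 + 0.20p)).

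**Conclusion.** The point holds as an optional improvement, not as an error that threatens the trial's conclusion. A baseline variable that eligibility leaves free to vary, known before allocation, is not used in the primary treatment comparison, and operative information is misplaced among the outcomes.

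Under the assumptions in step 2, adjustment removes about 1–14% of outcome variance and raises power at 41 per arm by between 0.6 and 6 percentage points (77.1 − 76.5 and 82.5 − 76.5). An imbalance of 10–20 points would move the unadjusted estimate by 0.5–3 points in either direction. An imbalance of at least 20 points has only a 4.9–7.1% chance with 50 per arm. If tear extent is weakly prognostic, or largely reflected in baseline WORC, the benefit is close to zero.

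**What to change.** Keep the eligibility criteria and the randomisation strata. Recruitment was under way when the article was submitted, and another factor would spread 100 patients over too many cells. Before the data are examined by arm:

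1. Add tendon involvement, as reported by the surgeon before allocation (supraspinatus alone v supraspinatus plus at least one other tendon), as a fixed factor in the primary WORC ANCOVA and in the strength ANCOVA. Add it to the multiple-imputation predictors too, so that the imputation and analysis models agree.
2. Move information from surgery out of the list of dependent variables and treat it as baseline data.
3. Tabulate tear extent by arm beside the re-tear results. Use it in the re-tear logistic model only as a sensitivity analysis, if the number of events allows.

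The cost is a few sentences and one degree of freedom per model, with no extra patients or procedures. The downside is little return if the factor proves weakly prognostic.

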### Blinding

Orthopedic surgeons will perform initial screening. As this is an “open-label” trial the health professionals delivering the interventions and the patients will not be blinded to treatment allocation. The principal investigator and outcome assessors will be blinded to treatment allocation during all pre-examinations and post-examinations, and patients are requested not to disclose their allocation when outcomes are assessed at weeks 6 and 12 and 12 months postoperatively. To test the efficacy of blinding, the outcome assessors are asked what treatment strategy they think a patient has received after assessments at week 12 postoperatively. The principal investigator and outcome assessors can be un-blinded if deemed necessary, e.g. in the case of (serious) adverse events that require these otherwise blinded persons to be involved in the solution of the event.

### Statistical analysis plan

The primary efficacy analysis performed is assessment of the between-group difference in change in the WORC score after 12 weeks in the ITT population. The ITT population is defined as all randomized patients irrespective of compliance or withdrawals. Missing data will be replaced using a multiple imputation technique with age, gender, center, group allocation (masked) and baseline values as predictors. For sensitivity purposes missing data will be imputed using baseline observation carried forward (BOCF). The modified ITT population is defined as the ITT population that has a valid baseline observation of the variable of interest. The as-observed (AO) population is defined as patients who have the outcome of interest assessed at a given time point of interest (i.e. no imputation of missing data will be done).

The per-protocol (PP) population is defined as patients in the AO population that adhere to this protocol, defined by the criteria of the two groups: the PR group (Table 1), included in the AO population and have attended at least 75% of the scheduled rehabilitation appointments, whether at clinical visits or home-based as tailored to the individual (documented by the exercise logbook), and do not stop the intervention during the 12-week main trial period and do not engage in concomitant exercise therapy (e.g. private physiotherapy sessions, acupuncture); and the UC group (Table 1), included in the AO population, and do not stop the intervention during the 12-week main trial period and do not engage in concomitant exercise therapy. Each patient registers the home shoulder exercises in an exercise logbook, and successful completion of the intervention is defined as performance of 75% of the planned exercises.

The primary analysis at week 12 will be by analysis of covariance (ANCOVA) on change from baseline in the WORC domains as dependent variables, with group allocation (two levels) and time (week 6 and 12), gender and site as fixed factors, whereas age and baseline values will be analyzed as covariates. Secondary outcome measures will be analyzed by multiple logistic regression for binary outcome measures (re-tear, tendon healing, recurrence of symptoms (e.g. pain and function), complications) and by ANCOVA for the continuous outcome measures (pain, patient-reported outcomes, surgery information, strength, ROM) as dependent variables (individually), with group allocation and time as fixed factors, and site and baseline values as covariates. Predictors of health outcomes will be analyzed by ANCOVA or multiple regression as independent variables, with change in the WORC as the dependant variable. All statistical tests will be two-sided and statistical significance will be denoted by a computed *p* value equal to or less than 0.05. All data analysis will be carried out according to a pre-established analysis plan. The statistical analysis plan (SAP) will be carried through blinded according to group allocation, and results will be interpreted in an author consensus statement prior to disclosing/revealing group allocation on the basis of a blinded review of the data from the primary endpoint (changes from treatment A compared to changes from treatment B), assuming that treatment A is the active treatment (PR), and the other assuming that treatment B is the active treatment (UC). Analysis of the primary outcome will be calculated blinded, and two interpretations will be performed based on whether PR or UC is superior. Not until signed consent from all of the authors of this trial (identical to the authors of this SAP) has been obtained, agreeing on one interpretation of the results only, will the randomization code be broken. This is to reduce bias in the interpretation of the current findings. On agreement, all members of the author group will approve and sign the interpretations before any publication procedures are initiated [76].

The protocol conforms to the recommendations of the Enhancing the Quality and Transparency Of health Research (EQUATOR) network [77] using the Standard Protocol Items: Recommendations for Interventional Trials (SPIRIT) checklist and the Consolidating Standards of Reporting Trials (CONSORT) statement [78] (Additional file 3).

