**Methods:**

The current study is a randomized, controlled, outcome-assessor blinded, multicenter, superiority trial with a two-group paralleled design. A total of 100 patients with surgically repaired traumatic rotator cuff tears will be recruited from up to three orthopedic departments in Denmark, and randomized to either a progressive early passive and active movement program or a limited early passive movement program (usual care). The primary outcome measure will be the change from pre-surgery to 12 weeks post-surgery in the Western Ontario Rotator Cuff Index questionnaire. Secondary outcomes include the Disabilities Arm, Shoulder and Hand questionnaire (DASH), range of motion, strength and tendon healing characteristics from ultrasound measurements at 12 months follow up.

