### Sample size and power considerations

The sample size is calculated to test the superiority of the PR protocol over the UC protocol in the assessment of change in the WORC physical symptoms subscale at week 12 (primary outcome) [75]. With 41 patients per group, the study will have 80% power assuming the expected group difference in the mean changes from baseline is 12 points, corresponding to the suggested minimum clinical relevant difference [47], the common standard deviation is 20 (0–100 scale) [75] and a significance level of 5%. With an expected dropout around 20% during the study we will randomize and allocate 100 patients (50 to each group); analyzing the intention to treat (ITT) population, which will give power of 85% to detect the aforementioned difference. A provisional deadline for patient recruitment is set to June 2018, but in case the target number of 100 patients has not been met the recruitment period may be extended to reach the number required (2 times 41 patients) to obtain power of at least 0.8 (80%).

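### BOCF, the imputation named for sensitivity, carries forward the unrepaired pre-surgery shoulder, so it is one extreme scenario and not a graded check of the primary multiple imputation

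*Protocol article*

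**What the plan says.** All places are in the protocol article.

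- Abstract, Methods, on the outcome: "The primary outcome measure will be the change from pre-surgery to 12 weeks post-surgery in the Western Ontario Rotator Cuff Index questionnaire".
- Patients and settings, on the timing of baseline: "a baseline assessment visit is performed between 1 and 14 days before surgery". Final inclusion waits until the surgeon has confirmed a complete, repairable supraspinatus tear.
- Allocation, randomization and sequence generation places randomization after both the baseline tests and the operation.
- Statistical analysis plan, on the population: "The ITT population is defined as all randomized patients irrespective of compliance or withdrawals".
- Same section, on the primary handling of missing data: "Missing data will be replaced using a multiple imputation technique with age, gender, center, group allocation (masked) and baseline values as predictors".
- Same section, on the check of that handling: "For sensitivity purposes missing data will be imputed using baseline observation carried forward (BOCF". No other imputation is named for sensitivity. An as-observed population is also defined, for which "no imputation of missing data will be done"; the per-protocol set is drawn from it.
- Sample size and power considerations: "With an expected dropout around 20% during the study we will randomize and allocate 100 patients (50 to each group".

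The article gives no mean 12-week recovery and no dropout rate by arm.

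**The concern.** The primary imputation conditions on group and baseline characteristics, so a patient lost from PR is filled in like comparable PR patients who stayed. That is a missing-at-random assumption, although the article does not use the term. A sensitivity analysis should show how far the result depends on it.

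BOCF gives each dropout zero change. In a trial whose baseline reflects current treatment, that may be a tolerable pessimistic guess. Here baseline is a torn shoulder and every randomized patient has since been repaired, in both arms. Zero change removes the recovery common to both arms as well as any benefit of PR. A patient with a week-6 WORC on file would still be given the pre-surgery value at week 12.

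At stake is the interpretation of the robustness check. Disagreement between BOCF and the primary result could reflect only which arm lost more patients, and so could agreement. Unequal loss is possible: the trial is open-label, and Interventions schedules three supervised sessions a week in PR against one in UC during weeks 2 to 5.

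**Working it through.** **Inputs from the article (Sample size and power considerations; Statistical analysis plan).** Difference d = 12, SD = 20, 50 per arm, two-sided 5%, dropout about 20%.

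**Assumptions, not in the article.** Mean UC change m = 0 to 40 points; dropout rates q_PR and q_UC; dropout unrelated to outcome within arm; SD 20 in both arms.

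**The plan's own figure.** SE = 20 × √(2/50) = 4.00; 12/4.00 = 3.00; power = Φ(3.00 − 1.96) = 85%. This reproduces the stated 85%, which counts all 50 per arm as fully informative.

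**BOCF contrast.** With dropouts set to zero, the arm means become (1 − q_PR)(m + d) and (1 − q_UC)m. Their difference is

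(1 − q_PR)d + (q_UC − q_PR)m.

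The first term is a shrunken effect. The second is the dropout gap times UC recovery and is present even when d = 0. The per-arm variance, with μ the arm's mean change, is (1 − q)·SD² + q(1 − q)·μ².

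**Equal dropout of 20%.** 0.8 × 12 = 9.6 whatever m is. The variance still grows with m. At m = 20 it is 320 + 0.16 × 400 = 384 in UC and 320 + 0.16 × 1024 = 483.84 in PR, so SE = √(867.84/50) = 4.17 and power = Φ(9.6/4.17 − 1.96) = about 63%. At m = 0 power is 75%; at m = 40 it is 46%.

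**Unequal dropout, true difference 12**

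| Dropout PR / UC | m | BOCF contrast | Power |
|---|---|---|---|
| 25% / 15% | 20 | 0.75 × 32 − 0.85 × 20 = 7.0 | 38% |
| 25% / 15% | 40 | 0.75 × 52 − 0.85 × 40 = 5.0 | 16% |
| 15% / 25% | 20 | 0.85 × 32 − 0.75 × 20 = 12.2 | 84% |
| 15% / 25% | 40 | 0.85 × 52 − 0.75 × 40 = 14.2 | 80% |

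**Unequal dropout, true difference 0.** The false contrast is (q_UC − q_PR)m.

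- PR 25% / UC 15%: −2 at m = 20 and −4 at m = 40. BOCF would wrongly favour PR in 0.7% and 0.3% of trials, against a nominal 2.5%.
- PR 15% / UC 25%: +2 and +4. BOCF would wrongly favour PR in 7.4% and 13.1%.
- m = 0: no false contrast in either direction.

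A simulated ANCOVA with baseline as covariate (m = 0, 20 and 30) showed the same pattern. At m = 20 and PR 25% / UC 15%, for example, it gave a contrast of 7.0 and power of about 40%. Baseline adjustment does not remove the extra term.

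**What a graded check would show.** Suppose an observed difference of 12 with 40 completers per arm and, conservatively, the complete-case SE: 20 × √(2/40) = 4.47. The 95% CI is 12 ± 8.77, or 3.2 to 20.8. With 20% missing in PR, lowering the imputed PR values by δ lowers the contrast by 0.20δ. Significance is lost at δ = 3.23/0.20, about 16 points. BOCF instead fixes the penalty at each arm's whole mean recovery: at m = 20, 32 points in PR and 20 in UC.

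**The case against.** The strongest points on the other side, and what stands of each:

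- **The primary inference does not use BOCF.** This stands. A reader might infer from the rejection rates above that the trial's type I error is inflated. The article does not support that: multiple imputation is primary, and no decision rule is attached to BOCF.
- **BOCF is itself an informative-dropout scenario.** This stands. One cannot say that the plan ignores informative dropout, only that it names a single extreme case that is neither plausible here nor graded.
- **The analysis plan may add more.** The article refers to a pre-established analysis plan that is not shown. A reader might infer that the trial has no tipping-point or similar analysis; that cannot be concluded. The point rests on the method the article does state.
- **The direction of dropout matters.** If PR's heavier visit schedule causes more loss in PR, and m is above zero, BOCF is conservative for a claim of PR superiority. False support for PR needs more loss in UC, for which the article gives no particular reason.
- **The size depends on assumptions.** Neither m nor dropout by arm is given. Slings are worn for five weeks and UC loading starts at week 6, so recovery at week 12 could be modest.
- **The 20% may overstate week-12 loss.** It is expected over the whole study, which runs to 52 weeks. With 10% in each arm, 12 shrinks only to 10.8. With PR 7.5% / UC 12.5% and no true effect, the false contrast is 1.0 (m = 20) or 2.0 (m = 40).

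The as-observed analysis does not answer the point. It imputes nothing and also treats dropout as uninformative.

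**Conclusion.** The concern holds as a cheap improvement. Because baseline precedes surgery and randomization follows the repair, BOCF answers a question mixed with completion rates and general post-operative recovery. Three statements are supported:

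1. With equal dropout, BOCF only attenuates the effect towards zero; this needs no assumption about recovery.
2. With unequal dropout and non-zero recovery, it moves the contrast by an amount unrelated to PR, in a direction set by which arm loses more patients. Its size depends on the assumed m and dropout rates.
3. If PR loses more patients, the main risk is failing to confirm a true effect. If UC loses more, BOCF can falsely support PR.

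The calculations take dropout as random within arm. They show how BOCF behaves when the primary assumption is true; they do not show that dropout in this trial will be informative or unequal.

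**What to change.** In the Statistical analysis plan section, replace the BOCF sentence with a sensitivity analysis built on the planned multiple imputation:

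- **Main sensitivity analysis.** Delta-adjusted imputation. Shift the imputed week-12 WORC change downwards over a grid in each arm separately (for example 0, 4, 8, 12 points and onwards until significance is lost) and report the tipping point. On the plan's own inputs the PR-only grid should extend beyond about 16 points.
- **Option.** Reference-based imputation, in which PR patients with missing week-12 data are imputed from the UC distribution.
- **BOCF.** Keep it only as a supplementary table, so that comparison with older trials stays possible.

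The primary analysis is unchanged. The cost is a wording change before the blinded analysis and a few extra runs on the imputed data sets, with no new patients or measurements. The one downside is that BOCF loses its interpretive weight. If the unseen analysis plan already contains such an analysis, it is enough to align the two documents.
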